## Abstract

**Background:**

Low back pain (LBP), with high incidence and prevalence rate, is one of the most common reasons to consult the health system and is responsible for a significant amount of sick leave, leading to high health and social costs. The objective of the study is to assess the cost-effectiveness and cost-utility analysis of a multidisciplinary biopsychosocial educational group intervention (MBEGI) of non-specific sub-acute LBP in comparison with the usual care in the working population recruited in primary healthcare centres.

**Methods/design:**

The study design is a cost-effectiveness and cost-utility analysis of a MBEGI in comparison with the usual care of non-specific sub-acute LBP.

Measures on effectiveness and costs of both interventions will be obtained from a cluster randomised controlled clinical trial carried out in 38 Catalan primary health care centres, enrolling 932 patients between 18 and 65 years old with a diagnosis of non-specific sub-acute LBP. Effectiveness measures are: pharmaceutical treatments, work sick leave (% and duration in days), Roland Morris disability, McGill pain intensity, Fear Avoidance Beliefs (FAB) and Golberg Questionnaires. Utility measures will be calculated from the SF-12. The analysis will be performed from a social perspective. The temporal horizon is at 3 months (change to chronic LBP) and 12 months (evaluate the outcomes at long term).

Assessment of outcomes will be blinded and will follow the intention-to-treat principle.

**Discussion:**

We hope to demonstrate the cost-effectiveness and cost-utility of MBEGI, see an improvement in the patients' quality of life, achieve a reduction in the duration of episodes and the chronicity of non-specific low back pain, and be able to report a decrease in the social costs. If the intervention is cost-effectiveness and cost-utility, it could be applied to Primary Health Care Centres.

**Trial registration:**

ISRCTN: ISRCTN58719694

## Background

Lower back pain (LBP), in any of its forms (acute, subacute, chronic), is one of the principal reasons for consulting the general practitioner (GP). The annual prevalence of LBP is estimated at 14.8% in a study carried out in the Spanish population [1], and these results were confirmed by the 2006 Spanish National health survey [2] and recent data from the Primary Care Information System of Catalonia [3].

LBP has an important impact in the performance of daily tasks and the quality of life of the individuals affected by this pathology. It also has social and family repercussions which are often ignored [1,4]. LBP is one of the six most frequent health problems in developed countries [5,6]. When the LBP diagnosis is established, the minimisation of disability and the cost of labour absenteeism constitutes a shared problem among patients, health professionals, business management, and administration, and makes early intervention necessary to avoid chronic LBP. Some epidemiological studies show that aspects such as psychosocial malaise and fear and avoidance behaviour are associated with a higher risk of developing incapacity in the long term. In patients with these characteristics, a cognitive behavioural intervention has been shown to be effective in reducing this risk [7,8]. Therefore, psychological and social factors associated with the symptoms should be considered because they could affect the level of pain and increase the risk of evolution to chronic LBP [9-12]. Failure to reduce pain represents an important increase in the economic cost to society and reduction in the quality of life of the patient [13,14].

The labour absenteeism caused by LBP is estimated at an average of 21.9 working days lost per illness episode, which represents a cost of 1260 € per worker per year [3]. This cost would be higher if the calculation also took into account "presenteeism" (reduced work productivity), which doubles or triples the cost of labour absenteeism alone [15]. Clinical practice guidelines include scant information about the cost-effectiveness of the treatments, except for those provided by the National Institute for Health and Clinical Excellence (NICE) [16]. In addition, the few studies published have important methodological limitations and are very heterogeneous, which limits the available evidence about the cost effectiveness of LBP interventions [17,18].

Given that the guidelines considered a range of interventions to be effective, it is important to assess the efficiency of treatments versus current intervention throughout the cost-effectiveness analysis [19-21]. As the number of published economic evaluations of interventions for LBP is increasing, it may now be possible to consider evidence of cost-effectiveness when making recommendations about treatment [15,22]. However, no studies have been identified that analyse the cost-effectiveness and cost-utility of multidisciplinary biopsychosocial interventions with respect to habitual practice in primary care.

The objective of the study is to assess from a societal perspective the cost-effectiveness and cost-utility of a multidisciplinary biopsychosocial educational group intervention (MBEGI) in comparison with the usual care of non-specific sub-acute LBP in the working population recruited in Barcelona and its surrounding Primary Health Care Centres (PHCC) since May 2009.

Secondary objectives are to identify and quantify the various costs associated with the disease and their distribution among all of the actors in society.

## Methods/Design

### Study design

Cost-effectiveness and cost-utility analysis of a cluster randomised clinical trial which compares patients with subacute non-specific LBP treated with a MBEGI approach, with a control group receiving only usual clinical care in PHCC. The analysis adopts the societal perspective because, it takes into consideration all other perspectives, will provide disaggregated data, and will make available the most extensive information for use in comparing studies [23].

### Setting (*)

The trial is being conducted in a primary care setting, in 38 PHCCs located in Barcelona, Spain and its surrounding areas. We contact all the PHCCs, present the study to their staff members and invite them to participate.

### Study population

Eligible patients will be identified by the GP or nurses when they consult for a new episode of sub-acute LBP or from searches of electronic clinical records. Patients are informed about the study objectives and those who agree to participate will be given written informed consent to sign.

Patients will be included if the current episode of LBP occurs suddenly after at least 6 months without LBP and lasts between 15 days and 12 weeks [24], and if they do not fulfil any of the exclusion criteria [20].

Furthermore, patients must be between 18 and 65 years old, understand Catalan or Spanish, and be available to participate for at least 12 months. Patients will be excluded if: (a) they are unwilling to participate in the multidisciplinary intervention trial; (b) LBP coexists with cognitive impairment, severe psychiatric disorders such as psychosis, or severe major depression; (c) any other cause of disability impedes answering the various questionnaires; (d) they are pregnant or breast-feeding; (e) they might have anti-inflammatory intolerance or allergy; (f) treatment has been received for physical problems in the preceding 3 months; (g) they have been referred for intensive functional restoration programmes; or (h) they have a confirmed diagnosis of fibromyalgia.

Furthermore, the GP has to ensure that the patient has no red flag signs or symptoms that are frequently associated with specific LBP or potentially severe illnesses [25-28].

### Randomisation

In this study a cluster design is used because the intervention is delivered to groups. To minimise contamination, the unit of randomisation will be the PHCC. Those PHCCs who agree to participate will be randomly allocated to control or intervention groups by a random sequence generated by a computer programme in blocks of random size and prepared before recruitment of the PHCC by an independent statistician who will be blinded to the PHCC identity. The blocking factor was a randomly selected even number (i.e., 4, 6, or 8) and will vary as the recruitment continues. GP or nurses will be informed about their allocation after giving final consent to participation.

To minimise imbalance across intervention groups, randomisation was stratified by percentage of immigrants from developing countries registered in each district. We consider two strata, less than and more than 15% immigrants. This variable is taken as a proxy of socioeconomic level.

### Blinding

During the recruitment, patients who meet the inclusion criteria are allocated to the intervention group corresponding to the centre. To avoid bias, consent to participate is obtained before the allocation. Because of the nature of the intervention, GPs or nurses cannot be blind to patients' allocation. Data analysis will be carried out so that the intervention groups allocated to the patients will be unknown to the analyst.

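### Consent before allocation is presented as a guard against bias, but the design implies that recruiting staff already know the arm when they invite patients

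*Protocol article*

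**What the plan says.** Four statements in the protocol article bear on the order of events.

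- Randomisation: "the unit of randomisation will be the PHCC", and "Those PHCCs who agree to participate will be randomly allocated to control or intervention groups". On disclosure, "GP or nurses will be informed about their allocation after giving final consent to participation".
- Study population: "Eligible patients will be identified by the GP or nurses when they consult for a new episode of sub-acute LBP"; searches of electronic records are a second route. Eligibility involves clinical judgement: "the GP has to ensure that the patient has no red flag signs or symptoms".
- Blinding: "patients who meet the inclusion criteria are allocated to the intervention group corresponding to the centre". The section accepts that GPs and nurses cannot be blind to the arm.
- Blinding, same paragraph: "To avoid bias, consent to participate is obtained before the allocation".

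In Statistical Analysis, the incremental cost-effectiveness and cost-utility ratios are differences in mean cost divided by differences in mean effect or QALYs. Multilevel regression is planned for the outcome scales, partly to adjust comparisons, with PHCC and individual as random effects and intervention and time as fixed effects. No baseline covariates are named for either analysis.

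**The concern.** In a trial that randomises patients one by one, consent before allocation conceals the arm from both the patient and the person recruiting. In a cluster trial, where the centre is randomised first and its own staff recruit afterwards, it cannot do the second job. Staff who know the arm may, without intending to, invite different kinds of patient: more motivated, more disabled, earlier in the episode, or more often on sick leave.

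Randomising centres does not balance such differences, because they arise after randomisation. Intention-to-treat does not help either, because it preserves the groups as recruited. The article's main results are cost and QALY comparisons, and for these it describes no baseline adjustment. A reader who takes the Blinding sentence at face value would believe that recruitment bias had been dealt with.

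**Working it through.** **Order of events.** The sections give this sequence:

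| Step | What happens | Section |
|---|---|---|
| 1 | PHCC agrees and is randomised | Randomisation |
| 2 | GPs and nurses give their own consent, then learn the arm | Randomisation |
| 3 | The same GPs and nurses identify patients and judge eligibility | Study population |
| 4 | Patient consents | Study population, Blinding |
| 5 | Patient takes the centre's arm | Blinding |

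There is no random step at step 5: the arm was set at step 1. The article does not tie disclosure at step 2 to patient recruitment. It also describes no blinded recruiter, no listing of patients before randomisation and no withholding of the arm from staff until patients are enrolled. That staff know the arm at step 3 is therefore an inference from the sequence, but nothing in the text contradicts it.

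**Possible meanings of the Blinding sentence.**

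1. The consent is that of the centre or its staff. This protects against selection of centres, not of patients.
2. The consent is the patient's, given before the patient is told the arm. This limits self-selection by patients. The recruiter's choice of whom to invite is untouched.

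Neither meaning gives concealment on the recruiter's side.

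**Why time since onset matters here.** Entry is allowed from 15 days to 12 weeks after onset (Study population), but follow-up is timed from onset (Data collection and information sources). Taking 3 months as 91 days, a patient entering at day 15 has 91 − 15 = 76 days before the 3-month assessment. One entering at 12 weeks has 91 − 84 = 7 days. An arm difference in time since onset would therefore change the treatment time before that assessment.

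**Scale.** First, the plan's own sample size, from the Sample size section (difference 2.5, SD 5.7, alpha 0.05 taken as two-sided, power 0.90, intraclass correlation 0.1, 25 per PHCC, 20% dropout):

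- n per arm before clustering = 2 × [(1.960 + 1.282) × 5.7 / 2.5]² = 109.2, rounded up to 110
- design effect = 1 + (25 − 1) × 0.1 = 3.4
- total = 2 × 109.2 × 3.4 / 0.8 = 929 (935 from the rounded 110)

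The stated 932 lies between these, so the figure reproduces and is not in dispute.

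At that size the standard error of the RDQ difference follows from 466 × 0.8 = 372.8 analysed per arm, or 372.8 / 3.4 = 109.6 effective: SE = 5.7 × √(2 / 109.6) = 0.77.

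If recruitment alone shifts the comparison by b points, the two-sided false-positive rate is 1 − Φ(1.96 − b/SE) + Φ(−1.96 − b/SE):

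| Assumed shift b (RDQ points) | Share of 2.5-point target | False-positive rate |
|---|---|---|
| 0 | 0% | 5% |
| 0.5 | 20% | about 10% |
| 1.0 | 40% | about 25% |
| 1.5 | 60% | about 50% |

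A shift of 0.5 would arise, for example, from a 1-point arm difference in baseline RDQ and a baseline-to-3-month slope of 0.5 (1 × 0.5), in a comparison of raw 3-month scores. In change scores the shift has the same size and opposite sign (0.5 − 1 = −0.5). The shifts and the slope are assumptions; none comes from the article.

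**The case against.** Several points on the other side are sound.

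- **The safeguard may be partly real.** A reader might infer that there is no protection at all. The article does not support that. Patients may well consent before being told their arm, which is a partial safeguard, so the sentence needs clarifying rather than simply deleting.
- **Recruiters' knowledge is inferred.** No single sentence says that staff know the arm when they approach patients. The inference is strong, but it should be worded as one.
- **Exclusion criterion (a).** One might argue that excluding patients because "they are unwilling to participate in the multidisciplinary intervention trial" screens differently by arm, since only intervention patients face 10 hours of sessions. The criterion is worded alike for both arms and refers to the trial. The argument requires patients to know their arm already, which the article does not say.
- **Analysis.** It would be wrong to say that all planned comparisons are unadjusted. The outcome scales have multilevel models intended to adjust comparisons, and the sample size rests on change in RDQ. The lack of stated baseline adjustment concerns the cost and QALY differences and the mean effects in the ratios.
- **Companion protocol.** The article refers to a separate effectiveness protocol that is not shown and may describe recruitment more fully. That could supply a safeguard, but the Blinding sentence as printed would still sit badly with the Randomisation and Study population sections.
- **Feasibility.** Recruitment has run since May 2009 and is described as under way, so replacing the sampling method would be a real mid-trial change.

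None of this restores concealment on the recruiter's side.

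**Conclusion.** The concern holds in a limited form. On the sequence the article gives, each patient's arm is fixed by the PHCC and, by inference, known to the recruiting GPs and nurses before the patient is approached. Consent before allocation therefore does not avoid recruitment bias. At best it limits self-selection by patients.

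The size of any bias cannot be estimated from the document. The RDQ figures above show only what assumed shifts would do. They apply to a comparison without baseline adjustment and use a normal approximation with the plan's own SD, clustering and dropout. A larger sample would not remove such a shift.

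The article does not establish that patients know their arm at consent, that the exclusion criteria act differently by arm, or that the outcome-scale analyses are unadjusted. The conclusion needs none of these.

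**What to change.** 1. **Reword the Blinding section.** State whose consent and which allocation are meant. If it is so, say that patient consent and baseline assessment are completed before the patient is told the centre's arm. State that recruiters are not blind to allocation, so recruitment bias is possible. This costs a few lines of text.
2. **Pre-specify baseline adjustment.** Use baseline RDQ, SF-12 utility, time since onset and sick-leave status in the cost, QALY and effect comparisons that feed the incremental ratios, and include the same covariates in the multilevel models already planned. The first-visit assessment and the eligibility check should already supply these values, so the cost is analysis time. Adjustment will not remove unmeasured differences such as motivation, and the report should say so.
3. **Report eligible, invited and consented counts per PHCC by arm**, where records allow. This fits the article's commitment to CONSORT for cluster trials. The cost is modest, though counts for patients already recruited may be incomplete.
4. **Optional, for remaining recruitment only:** use the electronic record search as a common sampling frame in both arms. This would change the recruitment method mid-trial and is not required to resolve the point.

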## Intervention Design

### Control group

Patients allocated to the control group will receive usual clinical care, and individual intervention based on the application of the "Clinical Practice Guidelines in the Pathology of the Lumbar Spine in Adults". These recommendations are published by the Catalan Institute of Health (*Institut Català de la Salut*) [25]. Details are given in Table 1.

**Table 1 T1:** Contents of the clinical guidelines applied in the cluster randomised trial

Clinical Practice Guidelines in the Pathology of the Lumbar Spine in Adults
■ Patient education, give reassuring and positive information about the benign nature of LBP, offer written information including specific advice.
■ Advise avoiding bed-rest and encourage the person to be physically active and continue with normal activities as far as possible.
■ Consider offering a structured physical exercise program tailored to personal preferences
■ Physical exercise should be introduced gently at first (walking, cycling, and swimming) and progressively increased in intensity.
■ Recommend attendance at the "Back School" to those patients who have not resumed their daily tasks, after six weeks.
■ Prescribe pharmacological treatment according to the established guidelines

Notes: LBP = low back pain.

### Intervention group

In addition to the same individual intervention as the control group, patients allocated to the intervention group will receive an educational booklet "The Back Manual" [29] (a transculturally adapted Spanish version of the Back Book) [30] and a biopsychosocial multidisciplinary group intervention.

The group intervention will be carried out by a GP, a nurse, a psychologist and a physiotherapist. The programme consists of 2 sessions of 4 hours duration each and 1 session of 2 hours duration. Each group includes up to 12 participants. Details of the MBEGI intervention and the educational digital video disc (DVD) are included in Tables 2 and 3.

**Table 2 T2:** Components of the biopsychosocial multidisciplinary group intervention

GP + Nurse 2 hours	Objective: Resolve doubts, demystify concepts about LBP and promote adherence to the intervention
	■ Basics on anatomy and biomechanics of the spine
	■ Pain mechanisms
Theory program	■ Causes of pain and predisposing factors
	■ Type of pain, mechanical, inflammatory, and severity
	■ Healthy life habits

Practical program	■ Discuss with the participants the doubts, beliefs and myths about back pain and give positive messages

**Physiotherapist** **4 hours**	**Objective: Provide tools on exercises/postures to avoid the pain and the chronic course and improve quality of life**.

	■ Body posture and its implication in pain
Theory program	■ Ergonomics
	■ Benefits of relative rest

	■ Diaphragmatic breathing exercises as the basis for relaxation, body awareness and postural control.
	■ Pelvic floor/gyration exercises.
Practical program	■ Propioceptive and posture awareness exercises.
	■ Strengthening exercises of the psoas and the posterior chain: Paravertebral muscles, gluteus, ischiotibial muscles.
	■ Strengthening exercises of abdominal muscles, specially the abdominal transversus, gluteus, spinal extensors and scapular muscles.

**Psychologist** **4 hours**	**Objective: Provide participants with cognitive-behavioural therapy techniques**

Theory program	■ Influences of cognitions, emotions and behaviour in pain

	■ Relaxation guidelines and methods
	■ Cognitive restructuring (Modulation of negative thoughts affecting emotions and pain)
	■ Use of attention (Increasing attention focus)
Practical program	■ Assertiveness (improving social relationships)
	■ Problem solving (training in step by step techniques for decision making)
	■ Time organization and reinforcement of reform activities and physical exercise.
	■ Life values (increasing concordance between values and behaviour) ■ Relapse prevention

Notes: GP = general practitioner; LBP = low back pain.

**Table 3 T3:** Contents of the educational Digital Video Disk

Contents of the educational Digital Video Disk
■ Basics on anatomy and biomechanics of the spine
■ Causes and mechanisms of pain
■ Recommendations on dealing with pain and coping with it in daily life
■ A series of stretching, strengthening, and flexibility exercises and methods to promote physical activity
■ Ergonomics applied to daily life (home, work and leisure)
■ Cognitive restructuring (Modulation of negative thoughts affecting emotions and pain)
■ Use of attention (increasing attention focus)
■ Assertiveness (Improving social relationships)
■ Problem solving (training in step by step techniques for decision making)
■ Time organization and reinforcement of reform activities and physical exercise
■ Life values (Increasing concordance between values and behaviour)
■ Relapse prevention

To guarantee the standardisation of the group sessions, only one qualified psychologist and one physiotherapist, both of them with extensive expertise in development of training groups, will apply the intervention in all PHCCs.

#### Outcomes

##### Effectiveness measures

The primary effectiveness measures of the study consist of Roland Morris Disability Questionnaire (RDQ) [31,32] (scale 0-24; lower score indicates lower disability), Mc Gill Pain Questionnaire [33-37] (including VAS 1-10; lower score indicates less pain), and Goldberg questionnaire on anxiety and depression. Duration of days of pain, the reduction of days off work, the reduction of prescription, the duration of pharmacological treatments and recurrent episodes of LBP and the incidence of chronic LBP at 12 months will be measured.

The secondary effectiveness measures are inadequate behaviour and work factors assessed by Fear Avoidance Beliefs Questionnaire (FAB) [38] (scale 0-24; lower score indicates lower fear-avoidance belief), and the Goldberg questionnaire of anxiety and depression [39] (each scale 0-9; lower scores indicates less anxiety or depression). All these questionnaires are validated in Spanish. Patient's assessment of global perceived effect on health will be measured by self-assessment with a Likert 7-point scale [40].

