##### Utility measures

The primary utility measure of the study is quality adjusted life years (QALYs), and will be calculated from the SF-12 scores (scale 0-100; lower score indicates poorer quality of life) [32].

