##### Sample size

The sample-size calculation is based on change in RDQ at 3 months after onset of LBP. It is recommended that a change of 2 to 3 points on the RDQ should be considered the minimum clinically important change [48]. To allow for the cluster randomisation by PHCC, we assume an intraclass correlation coefficient of 0.1 [49] and a minimum average number of individuals sampled per PHCC of 25. In order to detect a difference of 2.5 points between the two intervention arms with a standard deviation of 5.7 [48,50], an alpha error of 0.05, a beta error of 0.10, and a 20% dropout rate, a sample size of 932 subjects was required, 466 subjects per intervention arm. Therefore, the total number of PHCCs is 38 (19 in each group).

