##### Statistical Analysis

The effectiveness of the intervention will be analysed in accordance with CONSORT guidelines, extended to a cluster randomised trial. The analysis will be carried out according to the intention-to-treat principle. Cost, outcomes and use of resources will be reported as mean values with standard deviations for each intervention arm. Comparisons will be done between arms on characteristics of the study population. Mean differences between groups in cost, outcomes and resources, and 95% confidence intervals were calculated. If cost data do not conform to the assumptions for standard statistical tests, the non-parametric bootstrap method will be performed [51].

To address potential biases due to incomplete follow-up, we will analyse patients with complete data at all time points and those with data at any time point, using the multiple imputation approaches to replace missing values. Bias due to non-response will be assessed at each follow-up.

The temporal horizon of the study is 3 months because this is the time of change to a chronic stage and 12 months to evaluate the outcomes at long term.

The discount rate will be 3% [52] that is closest to the actual discount rate.

To establish an important change in individuals, we will contrast the distributions of changes in all the questionnaires and in each assessment, in individuals who change to chronic state and those who do not [48]. We will do the same between those individuals who return to work and those who do not. We will compare individual change scores to the standard error of measurement (SEM).

To detect changes in groups, the intervention effect will be calculated through the effect size for each questionnaire and at each assessment. Effect size will be calculated following the method of Kazis et al [53].

We will evaluate responsiveness of each scale by standardized response mean (SRM) [54] and receiver-operating characteristic method (ROC curve). Since the unit of randomisation is the PHCC, we will use a regression analysis of individual level data using methods for clustered data [55].

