To adjust comparisons and to account for cluster randomisation, multilevel linear regression analyses on repeated measures on each of the outcome scales will be used to assess the effect of intervention and to investigate the factors that influence each of the outcome scales at each time point. The possible association between intervention and time will be studied. The PHCC and the individual will be considered as random effects and intervention and time as fixed effects.

The incremental cost-effectiveness ratios were calculated as the difference in mean costs between the MBEGI and the usual care divided by the difference in mean effect, measured in natural unit, between MBEGI and the usual care.

Utilities will be calculated from the SF-12 scores with the corresponding Oxford University algorithm. The QALY will be calculated using these utilities, adjusted by time. The incremental cost-utility ratio will be calculated by dividing the difference in mean total costs between the MBEGI and the usual care by the difference in QALYs [56,57].

To determine the uncertainty surrounding these ratios, 95% confidence intervals for cost-effectiveness ratios will be calculated by the non-parametric bootstrap method [51].

Acceptability curves will be use to determine the probability that the MBEGI will be cost effective compared with usual clinical care at different values of the maximum acceptable ratio.

A deterministic sensitivity analysis will be performed to assess the robustness of the results [58]. The sickness days, GP visits and the number of medications will be measured to assess the impact on costs and cost-effectiveness. The discount rate will be 1% and 5%.

Confidence intervals around point estimates will be reported. The results will be presented in a disaggregated as well as aggregated form.

The significance level of all models will be set at 5%. The SPSS statistical package for Windows, version 19 (SPSS Inc., Chicago, IL) and the Stata/SE version 11·1 for Windows (StataCorp LP) will be used for statistical analysis.

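### The Goldberg questionnaire is classed as both primary and secondary, and RDQ at 3 months, the only result the trial is sized for, is never named as the single primary among several co-primary scales each set at 5%

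*Protocol article*

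**What the plan says.** In the protocol article, the Effectiveness measures section opens with "The primary effectiveness measures of the study consist of Roland Morris Disability Questionnaire (RDQ" and completes the list with "Mc Gill Pain Questionnaire [33-37] (including VAS 1-10; lower score indicates less pain), and Goldberg questionnaire on anxiety and depression". The next paragraph gives the secondary measures as the fear-avoidance questionnaire "and the Goldberg questionnaire of anxiety and depression [39] (each scale 0-9; lower scores indicates less anxiety or depression". The same instrument therefore has two statuses in adjacent paragraphs. The Utility measures section adds: "The primary utility measure of the study is quality adjusted life years (QALYs".

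The Statistical Analysis section sets two horizons and ranks neither: "The temporal horizon of the study is 3 months because this is the time of change to a chronic stage and 12 months", the latter for long-term outcomes. It plans a multilevel repeated-measures regression for each scale, partly "to investigate the factors that influence each of the outcome scales at each time point", and ends with "The significance level of all models will be set at 5" per cent. The cost-effectiveness ratio is defined with a difference in mean effect in natural units as denominator, but no particular effect is named.

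Only the Sample size section singles out one endpoint and one time: "The sample-size calculation is based on change in RDQ at 3 months after onset of LBP". It does not call this the primary outcome.

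**The concern.** An analyst cannot treat Goldberg as both primary and secondary, so one of the two sentences has to give way, and the article does not say which. Beyond that, three instruments carry primary status (four scores, if Goldberg anxiety and depression are taken separately), each modelled at 5%, with no statement of which result decides effectiveness.

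Two things are at stake. First, a favourable result on any one of these scales could be presented as the primary finding, although the trial was sized for one of them only. Second, the effect used in the headline cost-effectiveness ratio could be chosen, or given the emphasis, after the data are known.

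**Working it through.** **1. Which test does the sample size pay for?** Inputs from the Sample size section: difference 2.5, SD 5.7, alpha 0.05 (taken as two-sided), power 0.90, ICC 0.1, 25 patients per centre, 20% dropout.

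- Individually randomised, per arm: 2 × [5.7 × (1.960 + 1.282) / 2.5]² = 109.24, rounded up to 110.
- Design effect: 1 + (25 − 1) × 0.1 = 3.4.
- After clustering: 109.24 × 3.4 = 371.4 (or 110 × 3.4 = 374).
- After dropout: 371.4 / 0.8 = 464.3 (or 374 / 0.8 = 467.5, rounded up to 468) per arm.
- Total: about 929 to 936, against 932 stated.

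The stated figure is reproduced within rounding. A one-sided 0.05 would need only about 383 per arm and does not fit. The 932 therefore uses a full two-sided 0.05 on one test, RDQ change at 3 months.

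**2. Power of that test at 932.** Effective number per arm: 466 × 0.8 / 3.4 = 109.6. Standard error: 5.7 × √(2 / 109.6) = 0.770. Power: Φ(2.5 / 0.770 − 1.960) = 90.1%.

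**3. False-positive chance if any one primary scale may be claimed.** For k independent tests at 5%, the chance of at least one false positive is 1 − 0.95^k. With one test per scale:

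| Tests counted | k | Independent | Common correlation 0.5 | Common correlation 0.7 |
|---|---|---|---|---|
| RDQ, McGill, Goldberg | 3 | 14.3% | 12.5% | 11.0% |
| Goldberg as two subscales | 4 | 18.5% | 15.7% | 13.0% |

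The correlated columns come from simulating equicorrelated two-sided z-tests (400,000 draws). The correlations are assumptions; the article gives none.

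**4. If Goldberg were simply secondary.** RDQ and McGill would remain as two primaries: 1 − 0.95² = 9.8% under independence. Removing the double listing reduces the problem but does not end it.

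**The case against.** Several objections carry weight.

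- **The article does not lack a primary result altogether.** A reader might infer that it does. But the sample size makes RDQ at 3 months the de facto primary for effectiveness, and QALYs are expressly the primary utility measure, which matters in an economic evaluation. What is missing is the statement that RDQ at 3 months takes precedence over the other scales called primary.
- **The inflation depends on a success rule that the article does not state.** A 5% level per model does not say that one positive scale is enough. If all primaries had to succeed, the false-positive rate would not rise, although power would fall.
- **A much larger figure is tempting but not supported.** Counting four scales at two horizons gives 1 − 0.95⁸ = 33.7%. That needs eight separate, independent confirmatory tests. The repeated-measures model could give one intervention test per scale, and the same scale measured twice in the same patients is unlikely to be independent. At assumed correlations of 0.5 to 0.7, eight tests give 25.0% to 19.0%.
- **The economic estimates are not affected by alpha.** The article plans several ratios with bootstrap intervals and acceptability curves. These are estimates, and the risk there is selective emphasis.
- **A hierarchy may exist elsewhere.** The article refers to a separate effectiveness protocol, which is not at hand. This could answer the missing decision rule. It would not cure two conflicting statuses printed in this article.

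**Conclusion.** The point holds in a limited form. The double classification of Goldberg is a contradiction in the text and needs no assumption. The multiplicity part rests on stated features (several scales called primary, unranked horizons, 5% for every model, and a sample size that uses the full 0.05 on RDQ at 3 months), but its size is conditional. If success on any one primary scale could be claimed, with one test per scale, the false-positive chance is at most 14.3% or 18.5% under independence, and about 11% to 12.5% for three tests at assumed correlations of 0.5 to 0.7. It would be higher with separate tests at each horizon, but the article does not commit to those as confirmatory tests. It does not follow that the trial's error rate is wholly uncontrolled or that its economic intervals are invalid. The defect should be corrected, and it does not threaten the design.

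**What to change.** - Name change in RDQ at 3 months as the single primary effectiveness measure, tested at two-sided 5%, and as the base-case effect for the cost-effectiveness ratio.
- Keep QALYs as the primary utility measure.
- List the Goldberg questionnaire once, as secondary.
- Report McGill and all 12-month results as secondary, either in a fixed test order or as estimates with confidence intervals and no confirmatory claim.

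The Background dates recruitment from May 2009, so this changes outcome status in a running trial. It should be a dated amendment, made before any unblinded analysis, with the reason recorded. If the separate effectiveness protocol already sets a hierarchy, the amendment should cite it and agree with it.

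The sample size stays at 932 and RDQ power at about 90%. The cost is that McGill, whose primary listing is not itself contradicted, and Goldberg lose primary status. Keeping all three instruments as alternative primaries would cost more. With a Bonferroni split (0.05 / 3 = 0.0167 each), RDQ power at 932 falls to Φ(3.247 − 2.394) = 80.3%. Restoring 90% would need 141 × 3.4 / 0.8, about 600 per arm or 1,200 in all.
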